## Abstract

*Procrastination* is a widespread problem that is highly prevalent among the young adult population and is associated with several negative consequences. However, current evidence on the effectiveness of e-health interventions for procrastination either lack a comparison to an inactive control, do not include a student population or are of poor quality. This protocol describes the design of a trial that will overcome these limitations and examine the effectiveness of a guided internet-based intervention (*GetStarted*) to reduce problematic procrastinating behaviors in college students compared to a waitlist control. This study will be a two-armed randomized controlled trial with a calculated sample size of *N* = 176. Participants will be students from seven universities in the Netherlands. The intervention group will receive a four-week e-coach-guided intervention for procrastination. The waitlist control group will get access to treatment four weeks after randomization. Assessments will take place at baseline, post-test (4 weeks post-baseline) and follow-up (6 months post-baseline). Data will be analyzed with an intent-to-treat principle. The primary outcome is change in procrastination behaviors measured on the Irrational Procrastination scale (IPS). Secondary outcomes are depression, anxiety, stress, and quality of life. Additionally, sociodemographic characteristics of the participants, satisfaction with treatment, program usability, satisfaction with e-coach and treatment adherence will be examined as potential moderators. The results from this study can build evidence for the effectiveness of a guided internet-based intervention for treating procrastination in college students. Should it be effective, *GetStarted* could provide a flexible, low-intense and cost-effective treatment for procrastination and prevent common mental health problems in college students.

**Trial registration:**

This trial is registered at ClinicalTrials.gov Protocol Registration and Results System (Trial number: NCT05478096).

## Introduction

1

Procrastination, which refers to the process of voluntarily yet irrationally delaying an intended or necessary course of action (Steel, 2007), is a widespread problem that is highly prevalent among the young adult population (Beutel et al., 2016). It was previously estimated that 20 % of the adult population self-identify as chronic procrastinators (Ferrari et al., 2005). This rate is a staggering 50 % for university students across many countries and continues to increase (Solomon and Rothblum, 1984; Tice and Baumeister, 1997; Pychyl et al., 2000; Schouwenburg et al., 2004; Steel, 2007; Ozer et al., 2009). Chronic procrastination is associated with several negative consequences such as low self-esteem, excessive worrying, anger problems, shame, increased stress, depression, anxiety, and overall lower satisfaction with life (Sirois, 2007; Flett et al., 2016; Stead et al., 2010; Beutel et al., 2016). Apart from the negative psychological consequences, students who procrastinate have lower grade point averages (GPAs), assignment scores, and examination scores when compared to those who do not (Tice and Baumeister, 1997; Steel et al., 2001; Kim and Seo, 2015). Subsequently, they experience adverse long-term consequences such as poor general health, problems in social relationships, financial struggles and limited career opportunities (Patrzek et al., 2012; Höcker et al., 2017; Stead et al., 2010). This indicates that students, in particular, could experience more negative consequences with procrastination compared to the adult population (Steel and Klingsieck, 2016).

Previous studies have suggested that there are treatments available to target procrastination in students, with cognitive behavior therapy (CBT) being the most effective treatment (van Eerde and Klingsieck, 2018). However, several barriers to seeking and receiving treatment need to be accounted for to implement treatment successfully. These barriers include underestimating the problem, fear of stigmatization, perceived lack of time, low financial resources, preference for self-management and low awareness of available resources (Czyz et al., 2013; Eisenberg et al., 2007). E-health interventions, which can be accessed quickly, anonymously, and on a flexible schedule, could be a possible cost-effective solution to several of these barriers (Andersson et al., 2014; Ebert et al., 2017). Studies examining the effectiveness of e-health interventions, specifically targeting procrastination, show that e-health is effective in reducing procrastination (Eckert et al., 2018; Lukas and Berking, 2018). For example, a recent randomized controlled trial showed that chat-based counselling was as effective as face-to-face counselling for reducing procrastinating behaviors (Gieselmann and Pietrowsky, 2016). In line with this, Rozental et al. (2018a), found that unguided internet-based treatment was as effective as a group-based treatment for procrastination. While these studies provide strong evidence for the effectiveness of e-health treatments for procrastination, they lack an inactive comparator to be able to distinguish the impact of these interventions precisely. Additionally, previous studies that have examined comparisons to inactive controls either lack a comparison to an e-health intervention, do not include a student population or are of poor quality with low sample sizes and a high risk of bias, specifically regarding blinding of outcome assessors (Rozental et al., 2018b). This warrants the need for high quality and adequately powered trial to test the effectiveness of an e-health intervention compared to an inactive control for procrastination among students.

Another important potential barrier to effectively treating procrastination is treatment adherence. Rozental et al. (2015a) found that many individuals who receive treatment for procrastination struggle to adhere to and keep up with treatment. Guided treatments have previously been shown to result in better treatment outcomes (Cuijpers et al., 2019). However, unguided treatments are more scalable and affordable (Fairburn and Patel, 2017; Karyotaki et al., 2017). One possible solution is guidance by non-clinicians, which has the promise to be equally effective compared to clinician guidance (Leung et al., 2022). Clinical psychology students, in particular, have successfully supported face-to-face interventions for academic procrastination (Wang et al., 2017). Our study employs trained clinical psychology students as e-coaches to guide the treatment. Should this be an effective form of guidance, it overcomes existing barriers of limited resources in the form of limited available psychologists and counsellors (Watkins et al., 2012). Additionally, it makes treatment more affordable as psychology students offer e-health guidance for significantly lower costs compared to licensed specialists.

Therefore, the present study aims to evaluate the effectiveness of a guided internet-based intervention for procrastination (*GetStarted*) in university students in the Netherlands. Furthermore, since procrastination is associated with various other psychological outcomes (Sirois, 2007; Flett et al., 2016; Stead et al., 2010; Beutel et al., 2016), we will evaluate the effect of this treatment on secondary outcomes such as depression, anxiety, stress, and quality of life. Finally, we aim to gather evidence for potential moderators to treatment effectiveness. These will be socio-demographic characteristics of the participants, satisfaction with treatment and e-coach, system usability and treatment adherence. This will be done to identify target groups that could benefit most from treatment. The main research question is whether *GetStarted* is effective in reducing problematic procrastinating behaviors in university students compared to a waitlist control. The secondary research questions include: What are the effects of *GetStarted* on secondary outcomes of depression, anxiety, stress, and quality of life? Moreover, are there any moderators of treatment effectiveness?

## Methods

2

### Study design/setting

2.1

This study is a two-armed randomized controlled trial comparing the effectiveness of a guided internet-based intervention program, *GetStarted*, to a waitlist control receiving no intervention for four weeks. A flow chart of the recruitment process and treatment period based on the recommendations of the CONSORT 2010 statement is shown in Fig. 1. This study is conducted within the Caring Universities project. Caring Universities is a consortium of 7 universities in the Netherlands. The project is a part of the World Health Organization (WHO) World Mental Health International College Student Initiative (WMH-ICS) (Cuijpers et al., 2019), aimed at improving our knowledge of university students' mental well-being and subsequently offering accessible web-based interventions to students in need.

**Fig. 1 f0005:**
[figure not shown]
Participant flow diagram with targeted numbers.

The study protocol follows the recommendations of the SPIRIT 2013 Checklist for clinical trial protocols (Chan et al., 2013) and was approved by the Scientific and Ethical Review Board of all participating universities in the Netherlands: Vrije University Amsterdam, Leiden University, Maastricht University, and Utrecht University, Erasmus University, University of Amsterdam, Inholland University of Applied Sciences. The trial is registered on clinicaltrials.gov (NCT05478096) and is conducted and reported according to the CONSORT 2010 statement and the guidelines for executing and reporting research on internet-based interventions (Schulz et al., 2010; Proudfoot et al., 2011). The program (*GetStarted*) is administered in all the participating universities mentioned above.

### Participants

2.2

Participants are domestic or international undergraduate, graduate or PhD students enrolled in the seven universities mentioned above. They will be eligible if they (i) are aged 16 or older, (ii) are enrolled at one of the participating universities, (iii) have access to a computer, laptop, tablet or mobile device with internet access (iv) score 32 or above on the Irrational Procrastination Scale (IPS) and (v) provide informed consent. We used the cut-off score of 32 as a previous study successfully used it to identify individuals suffering from procrastination (Rozental et al., 2015b). Participants are excluded if they show any suicidal risk by identifying if they have had thoughts of killing themselves or have made plans of killing themselves in the past year and then responding to the question “How likely do you think it is that you will act on this plan in the next 12 months?” with: somewhat likely, likely or very likely. Recruitment started on 19th November 2021.

### Procedure

2.3

We recruit participants in three ways: First, via the yearly online survey of the WHO WMH-ICS that canvasses the mental well-being of students. All students at the participating universities receive this survey via email. At the end of the survey, students can choose to receive feedback on their mental health, and students who show increased procrastination tendencies (IPS ≥ 32) are invited to sign up for the GetStarted program. Second, marketing activities are conducted online via social media and on-campus via posters, flyers and other advertisements. Third, we recruit participants through the staff who work directly with students (e.g., student psychologists, study advisors and lecturers) by asking them to recommend it to the students who might benefit from the program. Eligible participants receive an email containing the details of the study and an informed consent form. Once informed consent is received, students are randomized to either the treatment or waitlist control group. Participants receive no compensation for completing the program. However, all participants who complete the screening, baseline and post-test questionnaires receive a shopping voucher of 10 euros for an e-commerce platform.

### Randomization

2.4

An independent researcher who is not involved in the study generates the random sequence using a computer random sequence generator. Randomization is at an individual level, stratified by university site and gender. Participants are randomized into two groups (web-based intervention vs WL) with an allocation ratio of 1:1. We conduct block randomization with randomly varied block sizes (6 to 12 allocations per block) to prevent foreknowledge of intervention assignment. The allocation is concealed to the study's researchers. However, it is not possible to mask personnel and participants to the treatment allocation because of the nature of the intervention.

### Intervention

2.5

*GetStarted* uses the evidence-based principles of cognitive-behavioral- therapy (CBT). It comprises five main modules and four optional modules that are all delivered via computer, laptop, tablet, or mobile phone (any device that allows internet access). The five main modules focus on the core mechanisms underlying procrastination that are relevant to all those struggling with procrastination. These modules employ CBT techniques and cover the following topics: The first module, through psychoeducation, offers an introduction to the process of procrastinating and an overview of the *GetStarted* program. It closes with a journaling assignment to help students identify procrastination behaviors associated with completing a current task. The second module, through psychoeducation and a journaling exercise, helps students understand the psychological mechanisms underlying procrastination and to recognize the positive and negative nature of procrastination. The third module focuses on unravelling cognitive distortions through exercises which allow students to identify the negative thoughts and feelings that accompany specific tasks, causing them to procrastinate. The fourth module helps students replace these unhelpful thoughts with helpful ones through a cognitive restructuring exercise in which they challenge their negative thinking patterns. This module also includes elements of behavioral activation where the student is encouraged to practice the process of ‘starting’ a task. The fifth and final main module encompasses relapses prevention where the student reflects on their progress, prepares for the future through goal setting techniques, and includes a summary of all the modules. Each module takes approximately 30–40 min, and students are advised to complete one module per week.

In addition to the main modules, students can choose to do all, any, or none of the four optional modules. These modules were made optional as they hold practical tools that may not be equally relevant to all students. Through behavioral activation and problem-solving exercises, the modules cover the following topics 1) breaking a big task into smaller parts, 2) creating and sticking to planning, 3) motivational techniques, and 4) increased productivity. All optional modules become available upon completion of the second main module. All nine modules consist of psychoeducation, reflection questions, interactive exercises, and homework assignments. The content is delivered textually and visually, including pictures, infographics and videos. The intervention is available to the participants on the caring universities platform (caringuniversities.com), which they can access anytime with their username and password. The duration of the program will be between approximately four and eight weeks. However, participants can follow the program at their own pace. Additionally, they are given the option to participate in the program anonymously.

#### Guidance

2.5.1

During the registration process, participants select an e-coach to support them during the program. The e-coach provides asynchronous, textual feedback via the platform within 72 h (counting workdays only) after every module completed by the participant. The aim is to increase motivation and adherence. E-coaches are (research) master students in clinical psychology and 3rd-year clinical psychology bachelor students (at the end of the 2nd semester) with specific knowledge of low-intensity treatment theory and skills. These coaches complete 6 h of training on their role as an e-coach, written language analyses, how to determine core messages, motivational interviewing techniques, good structure for feedback, crisis management, protocol adherence and several practice sessions before starting their coaching activities. Apart from this, they are required to attend weekly one-hour intervision meetings, which are supervised by the research team. Participants also receive automatic email reminders if they are inactive for 2 weeks without having finished the program.

### Control condition

2.6

Participants assigned to the wait list control group will receive no intervention for 4 weeks post randomization. During this time, they will be free to utilize any available usual treatment options such as GP's, student psychologists and academic counsellors.

### Assessments and outcomes

2.7

All assessments take place via the Caring Universities platform. At each time point, the participants receive a link to the assessment questionnaire via email. They get reminder emails to fill out the questionnaire 1 and 2 weeks after receiving the questionnaire. If they still don't fill it out, they will be called within a few days to remind them about the questionnaire. The reminder calls are made by the e-coaches, except for the anonymous participants who will be called by a researcher in the study. All outcomes and their time point measures are listed in Table 1.

**Table 1 t0005:** Time point measures of outcome assessments.

Outcome	Measure	Time of assessment					
		T0	T1	T2	T3	T4	T5
Socio-demographics	SR	X					
Procrastination	IPS	X		X	X	X	X
Depressive symptoms	PHQ-9		X	X	X	X	X
Stress	PSS		X	X	X	X	X
Anxiety	GAD-7		X	X	X	X	X
Quality of life	MHQoL		X	X	X	X	X
Satisfaction with treatment	CSQ-8			X		X	
Program usability	SUS-10			X		X	
Satisfaction with e-coach	WAI-I			X		X	
Treatment adherence	Number of modules completed		X	X	X	X	

Note: Abbreviations (alphabetical): CSQ-8: Client Satisfaction Questionnaire – 8 item version; GAD-7: Generalized Anxiety Disorder scale – 7 item version; IPS: Irrational Procrastination Scale; MHQoL: Mental Health Quality of Life questionnaire; PHQ-9: Patient health Questionnaire – 9 item version; PSS: Perceived Stress Scale; SR – self report measure; SUS-10: System Usability Scale – 10 item version; T0: eligibility screening – both groups; T1: baseline screening – both groups; T2: 4 weeks post baseline – intervention group; T3: 4 weeks post baseline – waitlist group; T4: 8 weeks post baseline – waitlist group; T5: 6 months post baseline – both groups; WAI—I: Working Alliance Inventory for guided internet interventions.

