#### Primary outcome

2.9.1

Change in procrastination scores on the IPS will be assessed at post-treatment and follow-up assessments using multilevel mixed models linear regression with a restricted maximum likelihood algorithm for normally distributed data. Binomial models will be used for skewed data. The post-treatment score will be used as the dependent variable and trial arm condition (web-based transdiagnostic intervention vs WL) as independent while adjusting for baseline IPS scores. We will calculate the effect size of Cohen's d by subtracting the intervention group's average score on IPS measures from the average scores of the control group at the post- treatment and dividing the results by the pooled standard deviations. In addition, we will calculate the means and standard deviations of the groups at all time points. Analogously, the Cohen's d will be calculated for the difference score between the post-test measurement (t3 for the intervention group and t4 for the wait list group) and follow-up assessment (6 months, t5).

The reliability change index (RCI) will determine clinically significant change (Jacobson and Truax, 1991). The RCI will be calculated using the standard deviations at baseline and the test-retest reliability coefficient of the IPS (Guilera et al., 2018; Rozental et al., 2014). Participants will be classified as improved, deteriorated or no change based on the RCI for pretest and posttest measures.

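### The only pre-treatment IPS is the screening score that selected students at 32 or more, which distorts the absolute RCI rates and within-arm change but not the randomised comparison

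*Protocol article*

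**What the plan says.** Section 2.7 states that "All outcomes and their time point measures are listed in Table 1". The table note separates two pre-treatment points, T0 for eligibility screening and a second one, "T1: baseline screening – both groups". In the table, the PHQ-9, PSS, GAD-7 and MHQoL are blank at T0 and marked at T1. The IPS, the primary outcome, is marked at T0, blank at T1, and marked again from T2 to T5. Section 2.3 also treats the two as different questionnaires: "all participants who complete the screening, baseline and post-test questionnaires receive a shopping voucher".

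The T0 score decides entry. Section 2.2 requires an IPS of at least 32, and in the survey route "students who show increased procrastination tendencies (IPS ≥ 32) are invited to sign up for the GetStarted program".

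Section 2.9.1 then relies on a baseline IPS in two places. The primary model takes the post-treatment score as dependent variable "while adjusting for baseline IPS scores". For clinically significant change, "The RCI will be calculated using the standard deviations at baseline" and the test-retest coefficient, and students are classified from pretest to posttest. Section 2.7.1 gives that coefficient as 0.84, from published work. No second pre-treatment IPS is described.

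**The concern.** Because T1 has no IPS, the score that selected the student must also serve as baseline and pretest. This has two consequences.

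- A score selected for being high is, on average, partly high by chance. It falls on remeasurement with no treatment and no true change.
- Cutting the distribution at 32 shrinks its SD. The RCI threshold is proportional to that SD, but the reliability of 0.84 comes from outside the selected sample. A restricted SD with an unrestricted r gives a threshold that is too small.

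The RCI is the article's only rule for clinically significant change, and the abstract describes the primary outcome as change in procrastination. Readers will look at improved percentages and at pre-post means in each arm. Both would show improvement that selection alone produces.

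**Working it through.** **The plan's own figure.** Per arm n = 2(1.96 + 0.84)² / 0.50² ≈ 63. With 28% dropout, 63 / 0.72 = 87.5, so 88 per arm and 176 in total. This reproduces section 2.8. It rests on an unadjusted t-test, so the choice of baseline IPS does not enter it.

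**Inputs from the article.** Cut-off 32, range 9–45, r = 0.84, RCI built from baseline SD and r.

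**Assumptions.** Source mean 26–34 and SD 5–7 before selection (no IPS mean or SD is given); a classical true-score model with independent errors; no true change; the usual RCI cut of 1.96 × SD × √(2(1 − r)), where √0.32 = 0.566.

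**Worked case: source mean 28, SD 6.** A whole-number score of 32 or more corresponds to 31.5 or more on a continuous scale.

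- Standardised cut = (31.5 − 28)/6 = 0.583; share eligible 0.28; mean T0 of those selected = 28 + 6 × (0.3365/0.2798) = 35.2.
- Expected fall = (1 − 0.84) × (35.2 − 28) = 1.15 points (simulation 1.17).
- The T0 SD among those selected is 2.97 (simulation), so the RCI cut is 1.96 × 2.97 × 0.566 = 3.3, meaning a change of 4 or more.
- SD of T0-to-post change: residual part 6 × √(1 − 0.84²) = 3.26; adding (0.16 × 2.97)² to its square gives 3.29.
- Improved: z = (3.5 − 1.16)/3.29 = 0.71, or 24%. Deteriorated: z = (3.5 + 1.16)/3.29 = 1.42, or 8%.
- With T1 as pretest, the SD of change is 6 × 0.566 = 3.39, centred at zero. With T1's own SD of 4.10 the cut is 4.5, so z = 4.5/3.39 = 1.33, or 9% each way.
- With the unselected SD of 6 the cut is 6.7, meaning 7 or more. From T0: z = (6.5 − 1.16)/3.29 = 1.62 and (6.5 + 1.16)/3.29 = 2.33, or 5% and 1%. From T1: z = 6.5/3.39 = 1.92, or 2.8% each way.

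**Simulation over the assumed grid, no true change.**

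| RCI pretest and SD | Improved | Deteriorated |
|---|---|---|
| T0, T0 SD (as written) | 11–37% | 6–12% |
| T1, T1 SD | 5–11% | 5–11% |
| T0, unselected SD | 3–6% | about 1% |

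The mean fall from T0 is 0.4–1.5 points (0.11–0.40 SD), and the T0 SD is 2.2–4.1 against 5–7 unselected. The top of the first row depends on rounding: about 33% if scores are rounded before the cut-off is applied, 37% if after.

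**Randomised comparison.** A null simulation of the adjusted model (mean 32, SD 6, 63 per arm, selection at 32) gave a mean treatment estimate of 0.01 and type I error of 0.045.

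**Precision.** The residual variance share, relative to the unselected variance, is 1 − r² = 0.294 with T0 alone. With T0 and T1 it is 1 − 2r²/(1 + r) = 1 − 1.411/1.84 = 0.233. The reduction is 1 − 0.233/0.294 = 21%, whatever the mean and SD.

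**The case against.** A reader might infer that the treatment effect itself is inflated. The article does not support that. The primary model compares arms on the post-treatment score, and Cohen's d at post-treatment is also between arms. Regression to the mean acts on both arms alike, and the waitlist shows its size. No within-arm pre-post test is planned; change from T0 appears only through descriptive means and SDs.

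A reader might also infer that the six-month follow-up result is inflated. Section 2.9.1 defines that d from post-test to T5. Its time labels differ from those in Table 1 and need reconciling, but neither labelling uses T0.

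The strongest objection concerns the remedy. Much of the misclassification comes from pairing a restricted SD with r = 0.84, and T1 scores are still restricted by selection. Adding T1 alone leaves the RCI miscalibrated, while keeping T0 with an unselected SD gives lower total misclassification and needs no new data. This stands, so the SD has to change as well.

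It is also fair that the precision case is modest. Over source means of 28–34, T0 leaves only 6–11% more residual variance than T1 would, with power at d = 0.50 of 0.94–0.98 against 0.96–0.99. The 21% needs both scores, and it shrinks if T0 and T1 errors are correlated or true scores drift. The T0–T1 interval is not stated.

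The blank T1 cell could be a slip in the table. Table 1 and section 2.9.1 would then still need to say which score is the baseline.

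**Conclusion.** The point holds for the absolute RCI rates and the descriptive within-arm change from baseline. It does not extend to the randomised contrast, the sample size or the post-test-to-T5 effect size. The direction follows from selecting on the same score that serves as pretest. The sizes rest on the assumed source mean and SD, and would be larger if the T0 score were old enough for its correlation with later scores to fall below 0.84. In every scenario examined, improvement is over-called relative to deterioration, and both exceed the nominal rate. RCI rates compared between arms share the artefact, so it is the absolute percentages that mislead. This is a cheap improvement worth making, not a threat to the main conclusion.

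**What to change.** - Add the nine-item IPS to the T1 questionnaire in Table 1, completed before randomisation. State in section 2.9.1 that T1 is the pretest for change scores and the RCI.
- Adjust the primary model for both T0 and T1 IPS.
- Compute the RCI with a reference SD from an unselected sample, preferably the one that yields r = 0.84. Cite it, and do not use the SD of the enrolled students.
- For students already enrolled without a T1 IPS, name T0 as the baseline, keep it in the model, and use the same reference SD. Read their RCI rates only as a comparison between arms.

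The cost is nine more items on an online questionnaire that students already complete, and a small amendment. The downside is that T1 IPS will be missing for students already enrolled (recruitment began in November 2021). The planned multiple imputation can keep them in one model, but it adds essentially no information about them.
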